## Visit 8: CHANGE IN MEDICATION USE

To be completed by study coordinator

Have you had any changes in medication use NOT related to your back pain in the past 7 days?

☐ No ☐ Yes (If YES, record below.)

| Medication | Indication* | Dose & Frequency | Start Date | Stop Date | Ongoing                  |
|------------|-------------|------------------|------------|-----------|--------------------------|
| 1.         |             |                  |            |           |  |
| 2.         |             |                  |            |           |  |
| 3.         |             |                  |            |           |  |
| 4.         |             |                  |            |           |  |
| 5.         |             |                  |            |           |  |

\*If Indication is related to a negative change in health status, alert study coordinator, complete Health Status Reassessment and enter in Adverse Event Log.

Notes:

Investigator Signature: \_\_\_\_\_

Date: \_\_\_\_\_

DAY-MONTH-YEAR

Participant ID # \_\_\_\_\_

Visit Date \_\_\_\_/\_\_\_\_/\_\_\_\_

## Visit 8: HEALTH STATUS REASSESSMENT

*To be completed by study staff*

Since your last visit, have you had any change in your health?

☐ No ☐ Yes (If YES, record below, alert study coordinator, and complete Adverse Event log.)

|                                                                                                                                            |                                                                  |
|--------------------------------------------------------------------------------------------------------------------------------------------|------------------------------------------------------------------|
| Change & Symptoms                                                                                                               |                                                                  |
| Describe:

Start Date:
Stop Date:
Missed work or school? _____ days | Treatment:

Outcome: |
| Change & Symptoms                                                                                                               |                                                                  |
| Describe:

Start Date:
Stop Date:
Missed work or school? _____ days | Treatment:

Outcome: |
| Change & Symptoms                                                                                                               |                                                                  |
| Describe:

Start Date:
Stop Date:
Missed work or school? _____ days | Treatment:

Outcome: |

**Investigator Signature:** \_\_\_\_\_

**Date:** \_\_\_\_\_

DAY-MONTH-YEAR

Participant ID # \_\_\_\_\_

Visit Date \_\_\_\_/\_\_\_\_/\_\_\_\_

## Visit 8: CONTRAINDICATIONS FOR LAB TESTING

To be completed by study staff

| Lab Testing Group        |                | Since your last visit have you had any of the following?                                                     |                                                             | If yes, describe and consult PI                                                                                                                                                                                                                                                                                                                                        |
|--------------------------|----------------|--------------------------------------------------------------------------------------------------------------|-------------------------------------------------------------|------------------------------------------------------------------------------------------------------------------------------------------------------------------------------------------------------------------------------------------------------------------------------------------------------------------------------------------------------------------------|
|  | 1 Muscular MRI | Contraindications for exposure to a magnetic field?
(Must complete Magnetic Field Contraindications form) |  Yes
 No |                                                                                                                                                                                                                                                                                                                                                                        |
|  | 2 Spinal MCL   | Muscle weakness in the legs?                                                                                 |  Yes
 No |                                                                                                                                                                                                                                                                                                                                                                        |
|                          |                | Episodes of incontinence of bowel or bladder?                                                                |  Yes
 No |                                                                                                                                                                                                                                                                                                                                                                        |
|                          |                | New or previously unreported muscle, bone or joint injury?                                                   |  Yes
 No | Date: _____                                                                                                                                                                                                                                                                                                                                                            |
|  | 3 Cortical TMS | Contraindications for exposure to a magnetic field?                                                          |  Yes
 No |                                                                                                                                                                                                                                                                                                                                                                        |
|                          |                | Migraine headache 6-months prior to V2 physiologic assessments?                                              |  Yes
 No | Administer ID Migraine Screener:
Sensitivity to light?  Yes  No
Nausea or vomiting?  Yes  No
Disabling intensity?  Yes  No
*if at least 2 symptoms, cancel TMS testing

Date of last migraine: _____ |
|                          |                | Taking medications in the benzodiazepine class?                                                              |  Yes
 No |                                                                                                                                                                                                                                                                                                                                                                        |
|                          |                | Recent concussion?                                                                                           |  Yes
 No |                                                                                                                                                                                                                                                                                                                                                                        |

If YES, describe in right column, refer to PIs, and complete Adverse Event Log (forms located in Appendix).

Investigator Signature: \_\_\_\_\_

Date: \_\_\_\_\_

DAY-MONTH-YEAR

Participant ID # \_\_\_\_\_

Visit Date \_\_\_\_/\_\_\_\_/\_\_\_\_

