### 7.1 Specification of Safety Parameters

At visits 2-9 the study staff will use the Health Status Reassessment CRF to ask the study participants if they have had any change in general health since the last visit. If fever or unexplained weight loss is reported, suggesting systemic infection / disease may be causing their low back pain, the clinician will do a basic physical exam and specifically assess for the possibility they have other systemic illness. They will be advised to seek medical care and research participation may be delayed, temporarily discontinued, or permanently suspended at the discretion of the examining clinician and in consultation with the Medical Directors if needed.

Before each treatment the study staff will use the Contraindications for Intervention CRF to inquire about change in back related signs indicative of increased severity of symptoms. Specifically if they have any increases in 1) radiating pain (i.e., burning, numbness, tingling sensations into the legs), 2) have noticed any muscle weakness in the legs, and 3) have any episodes of incontinence of bowel or bladder. If the study participant reports yes on any of these items the clinician will do a basic physical exam and assess neurological function by checking

myotomes, dermatomes, and reflexes to determine whether the study participant now presents with hard neurological signs (e.g., loss of motor function, significant changes in reflexes), or symptoms of other systemic disease. If the participant does present with hard neurological signs or serious systemic disease, they will be encouraged to seek consultation with their personal physician, and they will be excluded from further participation from the study.

Before each experimental measurement lab testing session (Visits 2, 8, and 9) the study staff will use the Contraindications for Lab Testing CRF to inquire specifically about symptoms of health issues contraindicated for the allocated experimental measurement lab test. Migraine headache will be assessed using The ID Migraine™ self-administered screener. If a possible contraindication is identified the PIs are consulted to determine safety before the lab testing begins.

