All negative changes in health status will be recorded as Adverse Events, logged, and reported per requirements of the Ohio University IRB and NIH-NCCIH. In the case of dismissal from the protocol for the above stated reasons, the Medical Safety Committee will meet to determine whether the AE was caused by the intervention (Definite, Probable, Possible, Unknown) and an adverse event report will be filed according to the specific requirements of the Ohio University IRB and NCCIH.

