## ID Migraine Screener

---

*To be completed by participant if migraine headache reported*

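### The Visit 8 and Visit 9 lab-testing forms ask about migraine before Visit 2, so the TMS migraine question misses the period since the last stimulation

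*Supplement*

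**What the plan says.** Protocol section 4.2 excludes from Experiment 3 anyone with a migraine in the 186 days before Visit 2 physiological testing. Section 7.1 then has staff complete the Contraindications for Lab Testing form before every lab session (Visits 2, 8 and 9). It adds that "Migraine headache will be assessed using The ID Migraine" screener, and that "If a possible contraindication is identified the PIs are consulted to determine safety before the lab testing begins".

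On the Visit 8 and Visit 9 forms the question column is headed "Since your last visit have you had any of the following". The migraine row beneath it reads "Migraine headache 6-months prior to V2 physiologic assessments", the same text as on the Visit 2 form. The cell for a positive answer holds the three ID Migraine items, an instruction to cancel TMS if at least two symptoms are present, and a space for the date of the last migraine. The other TMS rows concern the present or recent past, for example "Taking medications in the benzodiazepine class". The stand-alone screener in the CRF appendix is labelled "To be completed by participant if migraine headache reported".

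**The concern.** The row's period ends at Visit 2 and the heading's period begins after it, so both cannot apply at Visit 8 or Visit 9. Taken at its word, the row repeats an eligibility question that was settled before the first stimulation and leaves out everything since.

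The plan itself treats migraine as a reason to review or cancel TMS, and the consent checklist names headache among the TMS risks. Before repeat stimulation, staff need to know whether a migraine has occurred since the previous session. As written, that depends on how each staff member resolves a contradictory row, or on the participant mentioning migraine in answer to a general question about health.

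**Working it through.** No power or alpha figure is involved. The check compares the recall periods of the forms with the visit schedule.

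**Rows on the Visit 8 and Visit 9 form.** MRI 1 + spinal 3 + TMS 4 = 8. Rows tied to the time before Visit 2: 1, the migraine row.

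**Timing inputs.**
- Visit 8 is 3 ± 1 days after Visit 7 (section 3, Study Duration), or 3 ± 2 days for the physiological measures (section 6.2.4).
- Section 6.2.4 puts Visit 8 at days 23 to 25 and Visit 9 at days 57 to 61.
- Visit 9 is also given as 28 ± 4 days after Visit 7 (sections 3 and 6.2.4).
- Assumption: Visit 2 is day 1. Visit 7 then falls on about day 21 (23 − 2 and 25 − 4 both give 21).

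**Intervals.**
- Visit 7 to Visit 8: 2 to 4 days, or 1 to 5 days by the wider window.
- Visit 2 to Visit 8: 23 − 1 = 22 to 25 − 1 = 24 days. By the wider window, Visit 8 is at days 22 to 26, which gives 21 to 25 days.
- Visit 2 to Visit 9: counted from Visit 7, days 21 + 24 = 45 to 21 + 32 = 53, so 44 to 52 days. By the stated study days, 57 − 1 = 56 to 61 − 1 = 60 days. The two schedules disagree, so the full range is 44 to 60 days.

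**What the migraine row covers.**

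| Reading | Visit 8 | Visit 9 |
|---|---|---|
| Row wording | no day after Visit 2 | no day after Visit 2 |
| Column heading | back to Visit 7: 2–4 of 22–24 days (or 1–5 of 21–25) | back to Visit 8 |

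Under the heading, Visit 9 is covered adequately. At Visit 8 most of the time since the first TMS session is still outside the question, because the checklists for Visits 3 to 7 include no lab-testing form.

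**Other routes by which a new migraine could surface.**
- *Health Status Reassessment.* It asks about any change in health since the last visit at every visit from 2 to 9, so it spans the whole period. Section 7.1 adds that "All negative changes in health status will be recorded as Adverse Events". The form does not name migraine and carries no instruction to cancel TMS.
- *ID Migraine screener.* Its look-back is 3 months, about 91 days, which exceeds 60. Given to everyone at each session, it would cover all of Visit 2 to Visit 9. On the lab-testing form its items sit in the cell for positive answers, and the appendix version is for reported migraine.
- *Change in Medication Use.* It refers a new indication reflecting worse health to the adverse event log, but its look-back at Visit 9 is 7 days, while Visit 9 comes weeks after Visit 8.

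**The case against.** The strongest reply is that the row agrees with the protocol. Migraine is tied to Visit 2 wherever it is defined as an exclusion, and the revision history shows that the anchor was chosen deliberately. Nothing in the documents expressly makes a migraine after Visit 2 a contraindication. The cancellation note also appears on the Visit 2 form, so its presence later may only show that a row was copied forward. This stands as far as eligibility goes. It does not explain why a form that section 7.1 requires again before Visits 8 and 9 should carry a live cancellation instruction behind a question that cannot detect anything new.

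A second reply is that staff would sensibly follow the heading and that other checks overlap. That is fair and limits the consequence. Section 7.1 can even be read as requiring the screener at every session. But the forms make it conditional on a positive answer or a reported migraine, the general health question does not lead to TMS cancellation, and following the heading still leaves Visit 8 reaching back only to Visit 7. That last limit belongs to the heading rather than to the migraine row alone.

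Two further points stand. The documents do not show that an intervening migraine makes repeat TMS unsafe; the consent checklist only lists headache as a side effect. And the forms shown are CRF version 5.0, while correspondence on protocol version 6.0 says the electronic forms were modified for the supplement. Those are not shown, so a later correction can be neither confirmed nor excluded.

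**Conclusion.** The concern holds, as a minor one. On the Visit 8 and Visit 9 forms shown, 1 of 8 rows asks about the wrong period, and it is the only migraine-specific question leading to PI review and TMS cancellation. By its own wording it covers no day after Visit 2.

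The day counts describe this row alone; they do not measure undetected migraines, since the Health Status Reassessment spans all of those days. The number missed is expected to be small and cannot be estimated from the documents. The conclusion rests on the version 5.0 forms being in use and, for the day counts, on taking Visit 2 as day 1.

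**What to change.** On the Visit 8 and Visit 9 forms, reword the row to ask about *migraine headache since your last lab testing session*, naming Visit 2 on the Visit 8 form and Visit 8 on the Visit 9 form. A positive answer should lead to the ID Migraine screener and PI review before TMS. Naming the lab session instead of the last visit brings the interval from Visit 2 to Visit 7 into the Visit 8 question.

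If late disclosure of an older migraine should also be caught, add a phrase for previously unreported events, following the injury row on the same form ("New or previously unreported muscle, bone or joint injury"). If the current electronic forms already do this, confirming it is enough.

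The cost is one row reworded on two forms, plus an occasional cancelled TMS session and hence a missing cortical measure at OA3 or OA4.

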## Visit 8: CONTRAINDICATIONS FOR EXPOSURE TO A MAGNETIC FIELD

*To be completed by study coordinator for MRI & TMS Lab Testing*

Do you have any **non-removable** metal or foreign objects in your body such as Cardiac Pacemaker, Cardiac Valve Replacement, Brain Aneurysm Clip, Shunt, Aortic Clip, Surgical Clips, Implanted Neurotransmitter, Insulin Pump, Infusion device, or internal hearing aid such as Cochlear implant?

- ☐ Yes (if yes, indicate on Medical History – Summary, exclude from TMS & MRI lab testing)  
☐ No

Do you have any **removable** metal or foreign objects in your body such as piercings, hearing aids, or prosthetic devices?

- ☐ Yes (alert lab) ☐ No

Do you have any joint replacements, metal rods, plates, screws, or nails in your body?

- ☐ Yes (alert lab and complete below) ☐ No

Surgery:  
Date:

Surgery:  
Date:

Surgery:  
Date:

Do you have any foreign objects in your body such as shrapnel, bullet, an eye injury involving metal or do you work with metal occupationally?

- ☐ Yes (alert lab) ☐ No

Investigator Signature: \_\_\_\_\_

Date: \_\_\_\_\_

DAY-MONTH-YEAR

## Visit 8: NUMERIC PAIN RATING SCALE

To be completed assessment team investigator

[figure not shown]

### Instructions:

Sometimes it is helpful to think about the Numeric Rating Scale in the following manner:

- 0 = No Pain
- 1-3 = Mild Pain (nagging, annoying, interfering little with your activities of daily living)
- 4-6 = Moderate Pain (interferes significantly with your activities of daily living)
- 7-10 = Severe Pain (disabling; unable to perform your activities of daily living)

Please indicate:

- What number would you give your pain right now?
- What number would describe your pain since your last visit?

Since your last visit how would you answer the next 3 questions:

What number on a 0 to 10 scale would you give your pain when it is the worst that it gets?

- What number on a 0 to 10 scale would you give your pain and when it is the best that it gets?
- At what number is the pain at an acceptable level for you?

Investigator Signature: \_\_\_\_\_

Date: \_\_\_\_\_

DAY-MONTH-YEAR

Participant ID # \_\_\_\_\_

Visit Date \_\_\_\_/\_\_\_\_/\_\_\_\_

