Study Duration: The study duration for an individual participant with low back pain is ~ 8 weeks. Specifically, we expect that the typical amount of time between the event of enrollment ascertainment and randomization will be 3-5 days (maximum 7), and that randomization will occur when study participants begin a study intervention (visit 2). The study intervention will occur over a 3-week period followed by approximately 4-week follow-up. Thus, in total the study duration for an individual participant will be ~ 8 weeks. Specifically, in the first visit we will obtain informed consent and conduct a screening exam to determine if candidates meet the inclusion/exclusion criteria for a given experiment. If subjects meet the inclusion/exclusion criteria for an experiment they will be enrolled into the study and allocated to one of three experimental measurement groups (i.e., Muscular, Spinal, or Cortical). At the second visit, participants will then be randomized to an intervention arm (i.e., mobilization, manipulation, or laser), baseline assessments of both clinical and physiological outcome measures will be obtained, a treatment intervention will be performed, and clinical and physiological outcome measures will be repeated (i.e., follow-up assessment). Participants will then undergo an additional five treatments over the next three weeks (visits 3-7; total treatments: 6; treatment frequency: 2x/week). It should be noted that following treatment 1 we will assess expectancy and credibility expectations for the respective treatment intervention. Three days +/- 1-day after the final treatment, subjects will report back to the laboratory for a follow-up assessment of the clinical and physiological outcome measures (visit 8). Lastly, to determine the long-term effects of the interventions, subjects will report back to the laboratory approximately 4 weeks (28-days +/- 4-days) after their last treatment for the final follow-up assessment of the clinical and physiological outcome measures.

(visit 9). The study duration for a participant in the healthy control group is 3-hour including screening, baseline assessments, and lab testing. The anticipated duration for the RELIEF Study is 5-years. We anticipate the total enrollment time to take up to 4 years (48 months). The required monthly enrollment rate for study completion in the proposed time frame is 3.4 subjects/month.

Randomization, Stratification, and Blinding:

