#### RCT Component

To test the following RCT hypotheses, we will collapse the clinical outcome data across the three physiological outcome groups. Our Co-Primary Outcomes are NPR and RMDQ scores. The NPR and RMDQ are classic measures for the assessment of pain and disability in low back pain. Our secondary outcomes are change in PROMIS measures of Pain Behavior, Pain Interference, Pain Intensity, and Physical Function. Our primary endpoint is OA3 (visit 8, 3-days +/-1-day after completion of course of treatment intervention).

- Primary Hypotheses
  - We hypothesize that the Manipulation and the Mobilization groups will display a significantly lower NPR level than the Sham Control at the post-treatment measure (OA3, our primary endpoint) after controlling for the baseline value. Because we have a directional hypothesis, we will use a one-tailed test.
  - We hypothesize that the Manipulation and the Mobilization groups will display a significantly lower RMDQ level than the Sham Control at OA3 after controlling for the baseline value. Because we have a directional hypothesis, we will use a one-tailed test.
- Secondary Hypotheses
  - We hypothesize that the Manipulation and the Mobilization groups will display significantly lower levels in PROMIS Pain Behavior, Interference, Intensity, and/or Physical Function than the Sham Control at OA3 after controlling for the baseline value.

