### RCT Component

#### Co-Primary Outcomes:

- Change in Numerical Pain Rating (NPR) score for average over the last 7-days
- Change in Roland Morris Disability Questionnaire (RMDQ)

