#### Secondary Outcomes:

- Change in PROMIS Pain Behavior
- Change in PROMIS Pain Interference
- Change in PROMIS Pain Intensity
- Change in PROMIS Physical Function
- Change in NPR scores for current pain, and worst and best pain in the last 7-days

The primary endpoint will be OA3.

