### Instructions:

Sometimes it is helpful to think about the Numeric Rating Scale in the following manner:

- 0 = No Pain
- 1-3 = Mild Pain (nagging, annoying, interfering little with your activities of daily living)
- 4-6 = Moderate Pain (interferes significantly with your activities of daily living)
- 7-10 = Severe Pain (disabling; unable to perform your activities of daily living)

Please indicate:

- What number would you give your pain right now?

- What number would describe your pain over the last 7 days?

Since the onset of your low back pain how would you answer the next 3 questions:

- What number on a 0 to 10 scale would you give your pain when it is the worst that it gets?
- What number on a 0 to 10 scale would you give your pain and when it is the best that it gets?
- At what number is the pain at an acceptable level for you?

Investigator Signature: \_\_\_\_\_

Date: \_\_\_\_\_

DAY-MONTH-YEAR

Participant ID # \_\_\_\_\_

Visit Date \_\_\_\_/\_\_\_\_/\_\_\_\_

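### The 7-day pain rating that defines the co-primary endpoint is not asked at Visit 8, the primary time point; the form there asks about pain since the last visit, 2 to 4 days on schedule

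*Supplement*

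**What the plan says.** The Précis and section 9.4 define the pain co-primary as "Change in Numerical Pain Rating (NPR) score for average over the last 7-days". The list in section 3 drops the word for average but keeps the 7-day window. Section 9.1 fixes the time: "Our primary endpoint is OA3 (visit 8, 3-days +/-1-day after completion of course of treatment intervention". Section 3 (Study Duration) agrees: "Three days +/- 1-day after the final treatment, subjects will report back to the laboratory for a follow-up assessment".

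The forms are in Case Report Forms v5.0. The pre-treatment form at Visit 2, which supplies baseline, asks "What number would describe your pain over the last 7 days", and Visit 9 (OA4) repeats that item. Visit 8 asks for current pain and then "What number would describe your pain since your last visit". The Visit 8 checklist lists one NPR form.

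The secondary outcomes include "Change in NPR scores for current pain, and worst and best pain in the last 7-days". At Visits 2 and 9 the worst and best items are introduced by "Since the onset of your low back pain how would you answer the next 3 questions". At Visit 8 they refer to the time since the last visit.

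Section 9.5 compares the NPR level at OA3 with sham, controlling for baseline, and treats a 2-point reduction as clinically meaningful. It gives no rule for building a 7-day value from the interval ratings.

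**The concern.** A co-primary endpoint should be collected as defined at the visit that decides the result. Here the primary visit departs from the definition, while the baseline and final visits follow it. A report that called the Visit 8 result a 7-day average would misdescribe it. A change score would subtract a 7-day recall from a recall of a few days. OA3 and OA4, which section 9.5 both analyses, would not be on the same footing. For worst and best pain, change from Visit 2 to Visit 8 could move without any change in the patient, because an extreme over a whole pain history is set against an extreme over a few days.

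**Working it through.** **1. The windows side by side.**

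| Source | Period-pain item | Worst/best items |
|---|---|---|
| Definition, section 9.4 | 7 days | 7 days |
| Visit 2, before treatment (baseline) | 7 days | since onset of back pain |
| Visits 3 to 7 (treatment) | since last visit | since last visit |
| Visit 8 (OA3, primary) | since last visit | since last visit |
| Visit 9 (OA4) | 7 days | since onset of back pain |

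Visit 8 carries the wording of the treatment visits. For worst and best pain, none of the forms matches the definition.

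**2. Length of recall at Visit 8.** The interval from Visit 7 is 3 ± 1 days, so 2 to 4 days. As a share of the declared window: 2/7 = 29%, 3/7 = 43%, 4/7 = 57%. Section 6.2.4 gives 3 ± 2 days for the physiological measures. On that window recall would be 1 to 5 days (1/7 = 14% to 5/7 = 71%), still short of 7. If Visit 7 was missed, which section 5.4 tolerates (5 of 6 treatments count as adherent), the recall is longer and varies between participants.

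**3. What this does to change and to the arm comparison.** Write the Visit 8 rating as Y8 = Y8(7-day) + δ, where δ is the shift from the shorter window. Its size and sign are not given in the documents.
- Change from baseline: Y8 − Y2 = [Y8(7-day) − Y2(7-day)] + δ. The shift stays in.
- Active minus sham at Visit 8: both arms answer the same item, so the difference in Y8 is a like-for-like comparison of pain since the last visit. It equals the 7-day effect only if mean δ is the same in both arms. A baseline covariate need not share the outcome's window.

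**4. The 2-point threshold.** Section 1.2 states it as a greater reduction than under sham. That reading compares arms on the same items and survives. Section 9.5 states it as a 2-point reduction. Read within a person, that mixes windows.

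**5. Worst and best pain.** The entry criteria require back pain for at least three months. The worst over that history will tend to be at least as high as the worst over 2 to 4 days, and the best at least as low. With no real change, worst pain would be expected to fall and best pain to rise from Visit 2 to Visit 8, in every arm.

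**6. What can be recovered.**
- PROMIS Pain Intensity has an average-pain item with a 7-day frame at Visits 2 and 8. It uses five verbal categories, not the 0-10 scale.
- Visits 7 and 8 both hold an interval rating, and the medication forms at both visits record days since the last visit. A day-weighted value is (d7·x7 + d8·x8)/(d7 + d8). Twice-weekly treatment gives d7 of about 7/2 = 3.5 days, so with d8 of 2 to 4 the pair covers about 5.5 to 7.5 days.

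**7. Power.** The plan's figure is not affected. With 54 × 0.9 = 48.6 per arm, d = 0.5 and one-sided 0.05, power comes to 0.794 against the stated 0.80.

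**The case against.** The best defence is that the primary test is unharmed. It compares OA3 levels between arms with baseline as a covariate, and every arm answers the same question. That stands, and it limits the point. The RCT is also described as exploratory, the other co-primary (RMDQ) uses the same wording at Visits 2, 8 and 9, and PROMIS Pain Intensity already has a planned OA3 comparison.

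A reader might infer more than the documents support:
- *That the treatment comparison is biased.* A window shared by all arms does not by itself bias a randomised contrast.
- *That the score is inflated because a transient benefit peaks just after treatment.* Nothing in the plan shows this. Section 2.2 notes soreness that resolves within hours to days, which could push the other way.
- *That a 7-day value cannot be obtained at all.* The Visit 7 and 8 ratings together cover roughly a week. What is missing is a rule.
- *That worst pain improves by construction.* The Visit 8 days follow the baseline history and do not lie inside it, so the shift is expected, not guaranteed. Best pain would tend to move the opposite way. Neither item appears in the hypotheses of section 9.1 or the analyses of section 9.5.
- *That all 162 participants are affected.* The plan assumes 10% attrition, and Visit 8 forms from before v5.0 are not shown.

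**Conclusion.** The inconsistency is real. The 7-day NPR declared as co-primary is not directly measured at Visit 8. What is measured covers 2 to 4 days, provided that Visit 7 was attended and Visit 8 fell within ± 1 day. The harm is to what the endpoint is called, to change from baseline (including a within-person reading of the 2-point threshold), to the comparison of OA3 with OA4, and to change in worst and best pain. The baseline-adjusted comparison between arms is valid for pain since the last visit.

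It affects everyone assessed with this wording, a number that the documents do not establish. The forms shown are v5.0, while the protocol is v6.0. The correspondence sent with v6.0 mentions modified electronic forms for the supplement, but no later Visit 8 pain form is shown. If one with a 7-day item exists, the point falls for participants rated on it.

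**What to change.** Before unblinding:
1. Restate the co-primary as NPR since the last visit at Visit 8, adjusted for baseline 7-day NPR. Do not call it a 7-day average or a like-for-like change.
2. Prespecify two sensitivity analyses on data already collected: the PROMIS 7-day average-pain item at Visits 2 and 8 (supportive only, since it is a verbal category item), and the day-weighted combination of the Visit 7 and Visit 8 ratings.
3. Do not report Visit 2 to Visit 8 change in worst or best pain as a 7-day change. Report only differences between arms at Visit 8.

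Rewording the form should not be the main remedy. The correspondence in June 2016 describes testing of back-pain participants as nearly complete, and the supplemental appendix reports 18 of 27 men and 31 of 33 women tested in Experiment 2 (49 of 60). Replacing the item for the last few would put two instruments into one endpoint. If enough participants remain, add a 7-day item to the Visit 8 form alongside the existing one.

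The cost is an amendment to the endpoint wording and a little extra analysis. The price is a headline endpoint that covers a shorter period than the one declared.
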